### Randomization and allocation

Random numbers will be generated by an independent statistician ([name]) using SAS® 9.4 software (SAS Institute Inc., North Carolina, USA). Block randomization with randomly selected block sizes of either 2 or 4 will also be adopted to keep the number of participants in each group as equal as possible at all times with an allocation ratio of 1:1. Of the 60 total participants, 40 will be stratified by site subgroups (20 in Kyunghee University Korean Medicine Hospital and 20 in Wonkwang University Gwangju Medical Center, respectively) and the remaining 20 will be competitively recruited from both sites.

Sealed and opaque envelopes with random numbers will be prepared by the statistician and opened by a study coordinator after eligibility assessment. Participants will be allocated into either the verum or sham EA group in the order of giving the informed consents. The study coordinator will notify the allocated group to practitioners, who will be different from outcome assessors.

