### Concomitant treatments

Drugs, such as steroids or nonsteroidal anti-inflammatory drugs, herbal medications, acupuncture, moxibustion, or rehabilitation therapies for shoulder pain in stroke patients are allowed throughout the trial. However, all concomitant treatments for HSP should be maintained with the same dosage and regimen at least 2 weeks before enrollment until the last assessment. If necessary, the participant should take 2 weeks for a run-in period before enrollment. When there are significant changes of concomitant medications in an enrolled participant, he or she will be dropped out.

The typical care for cerebral hemorrhage or infarction, including oral medications (antiplatelet agents, anticoagulants, or neuroprotectants), rehabilitation therapies, traditional herbal medications, acupuncture, moxibustion, and EA therapies except for at the LI4, LI15, TE14, SI9, SI11, and GB21 acupoints will be permitted throughout the study for both groups.

All the treatments that the enrolled patients take will be monitored closely and recorded in case report forms. When any concomitant treatments related to shoulder pain are significantly different between groups, the findings will statistically be adjusted with these data of concomitant treatments.

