### Outcomes

#### Primary outcome

The VAS is a patient-rated outcome which has been validated for pain [18]. This scale is a 10-cm line where zero represents “not painful at all” and ten represents “most painful.” The patient marks an “x” on the line, based on how intense he/she thinks the pain is, and the assessor measures the length from zero to the “x” mark, which is the pain score. Many clinical trials for poststroke shoulder pain use VAS as their main outcomes [10]. In this study, VAS will be evaluated at every visit and the primary endpoint is defined as the mean change of VAS between the baseline and endpoint to show the intergroup difference. The mean differences of the before and after VAS scores within each group will be subordinately evaluated to see the intragroup effect.

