### Statistical analysis

A full analysis set is defined as a group of participants who receive 7 or more verum or sham EA sessions with an evaluation of the primary outcome at the endpoint, while a per protocol set is a subset of participants who complete all verum or sham EA sessions as planned in the protocol. We are going to statistically analyze the obtained data, primarily on the full analysis set, as well as, on the per protocol set for the efficacy analysis. Missing values will be imputed by the method of last observation carried forward in the full analysis set.

Demographic information will be tested with a two-sample t-test or Wilcoxon rank sum test for continuous variables and chi-squared test or Fisher’s exact test for categorical variables. When statistically significant differences between groups are found in demographic information, especially age and sex, those will be used as covariates for effectiveness analysis.

Primary and secondary variables will be summarized using the mean ± standard deviation and tested by two-sample t-test or Wilcoxon rank sum test depending on normality of the distribution. If concomitant treatments are significantly different between groups, intergroup effect will be tested by an analysis of covariance with the information of concomitant treatments adjusted. For the intragroup effect, the results of the VAS scores will be tested by paired t-test or Wilcoxon signed rank test. The significance level will be set at 0.05 (two-sided). Statistical analyses will be performed using SAS® 9.4 software (SAS Institute Inc., North Carolina, USA) by an independent statistician ([name]).

The number of adverse events will be presented with a 95% confidence interval on a safety set defined as a subset of participants who receive at least one verum or sham treatment. A chi-squared test or Fisher’s exact test will be carried out to compare the significant differences between groups.

The results of the blinding assessment will be presented as the number of participants per group assignment with the participants’ deductions of their group assignment in a 2 × 3 table. We will consider blinding to be successful in this study if the calculated confidence interval of the new BI includes zero, following the previous study [14].

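### The primary VAS test is picked by a normality check and significance-triggered covariates, and neither baseline VAS nor site is a covariate in any stated model

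*Protocol article*

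**What the plan says.** The Primary outcome section says that "the primary endpoint is defined as the mean change of VAS between the baseline and endpoint to show the intergroup difference". Under Power calculation the hypotheses are written in means, equal against unequal, two-sided. The Statistical analysis section then fixes the test: variables are "tested by two-sample t-test or Wilcoxon rank sum test depending on normality of the distribution". The article names no normality test and does not say on what the check is run.

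Two rules let covariates in, both conditional on a significance test. For demographics: "When statistically significant differences between groups are found in demographic information, especially age and sex, those will be used as covariates for effectiveness analysis". For other treatments: "If concomitant treatments are significantly different between groups, intergroup effect will be tested by an analysis of covariance". The Concomitant treatments section shows that the second rule draws on data from the whole trial: "All the treatments that the enrolled patients take will be monitored closely and recorded in case report forms".

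On allocation, the Randomization section states: "Of the 60 total participants, 40 will be stratified by site subgroups", 20 at each hospital, with the other 20 recruited competitively. No stated model contains site, and none has baseline VAS on its right-hand side.

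**The concern.** The article itself settles these rules, so this is not detail left to an analysis plan. Four things follow.

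- **The data choose the primary analysis.** The p-value may come from a t-test, a rank-sum test, or an ANCOVA with demographics, with concomitant treatments, or with both.
- **One branch answers a different question.** A rank-sum test addresses a difference in means only under an added assumption, such as a pure shift between arms, which the protocol does not make.
- **The triggers select on the wrong thing.** Under randomisation, a significant demographic difference shows chance, not prognostic value. The treatment trigger can also put a post-randomisation variable into the primary model.
- **Useful information goes unused.** A change score adjusts for baseline VAS with a slope fixed at 1. If the true slope differs, a chance imbalance leaves a residual bias and some precision is lost. Leaving out a stratification factor also loses precision.

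**Working it through.** **1. The plan's own figure.** Power calculation gives reductions of 3.52 (SD 2.67) and 1.38 (SD 2.43).

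- Difference: 3.52 − 1.38 = 2.14.
- Pooled variance: V = (2.67² + 2.43²)/2 = 6.517, so SD = 2.553 and d = 2.14/2.553 = 0.838.
- The noncentral t calculation gives 23.34, so 24 per arm, with power 0.811. Then 24/0.8 = 30 per arm, 60 in total.

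The stated sample size reproduces, and it matches an unadjusted t-test on change.

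**2. Plausible baseline spread.** Entry requires VAS of at least 4 on a 10-cm line, so baseline lies between 4 and 10. A uniform spread there has SD 6/√12 = 1.73. I take 1.25 to 1.73 as an assumed range. The baseline-endpoint correlation ρ is not in the document; I assume 0.3 to 0.7.

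**3. Gain from adjusting for baseline VAS.** Hold V at 6.517 and write b for baseline, f for endpoint:

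- SD_f = ρ·SD_b + √(V − SD_b²(1 − ρ²))
- variance ratio = SD_f²(1 − ρ²)/V
- slope of endpoint on baseline = ρ·SD_f/SD_b

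Example, SD_b = 1.25 and ρ = 0.7: SD_f = 0.875 + √(6.517 − 0.797) = 3.267; ratio = 10.67 × 0.51/6.517 = 0.835; slope = 0.7 × 3.267/1.25 = 1.83.

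| SD_b | ρ | slope | variance ratio | power, 24 per arm |
|---|---|---|---|---|
| 1.25 | 0.3 | 0.63 | 0.968 | 0.824 |
| 1.25 | 0.5 | 1.17 | 0.993 | 0.814 |
| 1.25 | 0.7 | 1.83 | 0.835 | 0.875 |
| 1.50 | 0.3 | 0.51 | 0.918 | 0.843 |
| 1.50 | 0.5 | 0.98 | 1.000 | 0.811 |
| 1.50 | 0.7 | 1.57 | 0.887 | 0.855 |
| 1.73 | 0.3 | 0.43 | 0.850 | 0.870 |
| 1.73 | 0.5 | 0.85 | 0.989 | 0.815 |
| 1.73 | 0.7 | 1.39 | 0.929 | 0.839 |

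The variance reduction is 0 to 17% and power is 0.81 to 0.875. Taking off two degrees of freedom lowers each power by less than 0.001.

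**4. Residual bias after a chance imbalance.** If verum starts higher by m cm, the change-score comparison shifts by m(1 − slope). Take an imbalance of 0.4 SD:

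- SD_b 1.73, ρ 0.3: 0.69 × (1 − 0.43) = +0.39 cm.
- SD_b 1.25, ρ 0.7: 0.50 × (1 − 1.83) = −0.42 cm.
- SD_b 1.50, ρ 0.5: essentially zero.

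The sign depends on the slope, and the planned effect is 2.14 cm. A significance gate would not help even if it were read to cover baseline VAS: at 24 per arm it reacts only above 2.013 × √(2/24) = 0.58 SD.

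**5. Normality gate.** Simulated at 24 per arm, 6,000 trials per scenario, with Shapiro-Wilk at 5% in each arm (an assumption):

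- Type I error of the gated test is 4.7 to 5.6% over normal and skewed scenarios.
- With normal data the gate switches tests in about 10% of trials. Run on pooled residuals instead, it switches in about 5%.
- Under the planned effect, the two tests disagree on significance in about 5 to 6% of trials with normal data and 9 to 11% with skewed data.

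**6. Covariate trigger.** For age and sex, if independent and each tested at 5%: 1 − 0.95² = 9.8% of trials would gain a covariate by chance.

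**7. Site.** With strata balanced and a site shift of 0.5 or 1.0 SD, ignoring site gives a type I error of 4.4% or 2.8%. Adjusting gives 5.1% in both cases.

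**The case against.** The strongest defence is that the planned test is valid, matches the sample-size calculation and already has the intended power. That stands. Several stronger readings are tempting, and the document does not support them.

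- **That baseline VAS is ignored.** It is subtracted from every value; it is only not used as a covariate.
- **That the plan inflates type I error.** The simulations show no gross inflation from the normality gate, and omitting site makes the test conservative.
- **That adjustment would save 15 to 35% of the variance, with power 0.87 to 0.94.** This assumes equal baseline and endpoint SDs. With the change SD at 2.553, the baseline SD must be 2.553/√(2(1 − ρ)), that is 2.16, 2.55 or 3.30 for ρ of 0.3, 0.5 or 0.7. On a range of 4 to 10, a unimodal distribution cannot exceed 2.0 and no distribution can exceed 3.0. One caution remains: the 2.553 comes from an earlier study whose entry rule is not shown.
- **That the last 20 allocations are unstratified.** The Randomization section says they are recruited competitively. It does not say how they are stratified.

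Two further points are fair. First, ANCOVA does not win everywhere: in the skewed scenario with ρ = 0.7 (simulated with equal SDs), the gated test had power 0.906 against 0.852. That gain comes from the rank test, which tests a different hypothesis.

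Second, treatments for the shoulder pain are supposed to stay constant, and significant medication changes lead to dropout. This narrows the route by which a post-randomisation variable enters, but does not close it: the trigger is not limited to baseline data.

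**Conclusion.** The concern holds as one of efficiency and prespecification. It is worth correcting but is not a validity error, and the sample size needs no change. The costs are a primary analysis that is not fixed in advance, a rank-sum branch that does not match the hypothesis on means, possible conditioning on post-randomisation treatment, and residual bias after chance baseline imbalance (up to about 0.4 cm for a 0.4 SD imbalance in the cases worked).

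The precision gain from baseline VAS is modest and may be nil: 0 to 17% of residual variance, with power of 0.81 to 0.875 against 0.811. That range rests on a change SD of 2.553, an assumed baseline SD of 1.25 to 1.73 and an assumed correlation of 0.3 to 0.7. Any gain from site is additional and depends on a site difference that the document does not give. The case for change therefore rests more on fixing one analysis than on power.

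**What to change.** Make the single primary analysis an ANCOVA of endpoint VAS (or change in VAS) on arm, with baseline VAS and site as prespecified covariates, reporting the adjusted mean difference and 95% confidence interval. Add age and sex only if they are judged prognostic in advance.

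Delete the normality gate and both significance-triggered covariate rules. Keep the rank-sum test and the adjustment for concomitant treatments as sensitivity analyses only.

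State whether the last 20 allocations are stratified by site. This is a clarification; no change to allocation is called for.

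The cost is analysis wording and about two degrees of freedom, with no extra patients or data. The trade-off is that under marked skew the primary test may have less power than a rank test would.

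### A between-arm p-value on concomitant treatment decides whether the primary comparison is adjusted, and the covariate is not limited to pre-randomisation use, so the adjusted effect can be biased

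*Protocol article*

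**What the plan says.** By default the primary and secondary variables are "tested by two-sample t-test or Wilcoxon rank sum test depending on normality of the distribution", with no adjustment. The Statistical analysis section then makes an exception: "If concomitant treatments are significantly different between groups, intergroup effect will be tested by an analysis of covariance". The Concomitant treatments section has its own version, limited to shoulder-pain treatments: "When any concomitant treatments related to shoulder pain are significantly different between groups, the findings will statistically be adjusted with these data". The data meant are described in the sentence before it: "All the treatments that the enrolled patients take will be monitored closely and recorded in case report forms".

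Three other statements bear on how far those records can change after randomisation:

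- Concomitant treatments requires that "all concomitant treatments for HSP should be maintained with the same dosage and regimen at least 2 weeks before enrollment until the last assessment". Item d of the Inclusion criteria makes agreement to this a condition of entry.
- The sanction is: "When there are significant changes of concomitant medications in an enrolled participant, he or she will be dropped out". Item e of the Dropout criteria also removes patients who take prohibited drugs or therapies.
- General stroke care (oral medication, rehabilitation, herbal medicine, moxibustion, and acupuncture or EA away from the six study points) "will be permitted throughout the study for both groups". No same-regimen wording is attached to it.

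**The concern.** Two things are wrong with the rule.

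**The trigger.** The observed data decide whether the main result is an unadjusted two-sample test or an ANCOVA. A covariate earns its place by predicting the outcome, which can be judged beforehand. A significant difference between randomised arms is not a reason to include it.

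**The timing of the covariate.** The records cover what enrolled patients take during the trial. Suppose sham patients improve less and some of them use more treatment. Use then depends on both arm and pain, and the rule is most likely to fire in just that case. Adjusting for such a variable does not correct a confounder, because randomisation has already dealt with confounding. It conditions on something that follows treatment, and it can move the estimate away from the effect of EA on VAS.

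At stake is the headline estimate for the primary endpoint.

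**Working it through.** **1. The plan's own figure.** Power calculation gives VAS reductions of 3.52 ± 2.67 and 1.38 ± 2.43, two-sided alpha 0.05 and power 0.8.

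- Difference = 3.52 − 1.38 = 2.14.
- Pooled SD = √[(2.67² + 2.43²)/2] = √6.517 = 2.553.
- Normal approximation: n = 2 × (1.960 + 0.842)² × 6.517 / 2.14² = 22.3, so 23 per group.
- t-test: power is 0.794 at 23 and 0.811 at 24, so 24 per group.
- Dropout: 24 / 0.8 = 30 per group, 60 in total.

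The stated sample size reproduces and is not in dispute. The difference of 2.14 is the true effect in what follows.

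**2. Regimen fixed before randomisation, as the protocol intends.** Simulation with 24 per arm, 6,000 trials, residual SD about 2.54 and binary concomitant use related to prognosis but not to arm. A Fisher test at p < 0.05 is the trigger; ANCOVA is used if it fires and the unadjusted comparison otherwise. The trigger fires in about 3% of trials. The rule's mean estimate is 2.15 against 2.14, and type I error is about 0.05. There is no bias, and the rule has no useful purpose.

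**3. Use that responds to arm and prognosis (assumed).** Same set-up, but use is lower in the verum arm and higher in patients who improve less. Use has no effect of its own on VAS. The unadjusted comparison gives 2.14 to 2.16.

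| Dependence on arm | Trigger fires | Rule's mean estimate | Shortfall from 2.14 | Power | Type I error under a true null |
|---|---|---|---|---|---|
| Weak | 11% | 2.11 | 2% | 0.80 | 0.050 |
| Moderate | 36% | 1.96 | 8% | 0.72 | 0.052 |
| Strong | 68% | 1.78 | 17% | 0.60 | 0.079 |

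Without the adjustment, power is about 0.81. If use also improves VAS by 1 point, the unadjusted total effect is 1.99, 1.89 and 1.76, and the rule gives 1.98, 1.85 and 1.69. The gap is then only 0.01, 0.04 and 0.07 points.

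**4. Use driven directly by each patient's VAS change (assumed).** 30 per arm, 4,000 trials per scenario. VAS reduction D is normal with mean 3.52 or 1.38 and SD 2.553. The probability of extra treatment is expit(a − bD).

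| b, a | Trigger fires | ANCOVA in every trial | Rule as written | Rule's shortfall |
|---|---|---|---|---|
| 0.3, 0 | 11% | 1.91 | 2.07 | 0.07/2.14 = 3% |
| 0.5, 0.5 | 23% | 1.67 | 1.94 | 0.20/2.14 = 9% |
| 0.8, 1 | 38% | 1.38 | 1.71 | 0.43/2.14 = 20% |
| 1.2, 2 | 48% | 1.15 | 1.49 | 0.65/2.14 = 30% |

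The last two columns describe the plan, which adjusts only when the trigger fires. In trials where it does fire, the unadjusted estimate averages about 2.5 and the reported adjusted one averages 1.95 down to 1.15.

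**The case against.** The strongest reply is that the protocol does not let shoulder-pain treatment respond to pain. It requires a stable regimen from two weeks before enrolment, with a run-in if needed, makes this an entry criterion, and drops patients whose medication changes significantly. Under that rule the covariate is essentially a baseline variable, and step 2 shows no bias. The scenarios in step 4 also sit badly with the protocol. They imply that 41 to 54% of sham and 25 to 28% of verum patients take extra treatment and still stay in the analysis, against a planned dropout of 20% from all causes. They also derive use from the outcome itself. Finally, a condensed article may leave the choice between baseline and on-trial records to an analysis plan not shown here.

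Much of this stands. A reader might infer from the rule that the primary result will certainly be biased, or that the effect will shrink by roughly 10 to 46%. The documents support neither. Stability is what the protocol requires. The larger range is the shortfall when ANCOVA is applied in every trial (1.91 to 1.15, or 10.7 to 46.3% below 2.14), which the plan does not do.

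The reply does not rescue the rule:

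- The drop-out sentence covers only changes judged significant, without defining the term, and it names medications, not rehabilitation or acupuncture.
- General stroke care carries no same-regimen requirement, and the trigger in Statistical analysis is not limited to shoulder-pain treatments.
- Dropping patients who change treatment is itself a selection made after randomisation.
- If regimens really are constant, a difference that fires the trigger is essentially chance, and its p-value is no basis for choosing the model.
- The trigger is stated outright in the article, so it is not a detail left to another document.

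**Conclusion.** The point holds as a fault in how the primary model is chosen, with bias as a conditional risk. If concomitant treatment stays constant, the rule is roughly unbiased and simply unnecessary. If use changes in response to treatment or pain, the rule can bias the effect, and in the scenarios examined it pulls it downwards.

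The documents contain no figures on concomitant use, so neither direction nor size can be fixed from them. The illustrative range for the rule as written is 2 to 17% below 2.14 with 24 per arm, and 3 to 30% with 30 per arm and use driven directly by VAS change. The upper ends need strong dependence, and the second range needs changes of treatment that the protocol tries to prevent. If the extra treatment itself relieves pain by 1 point, the rule differs from the unadjusted total effect by no more than 0.07 points. That the model is chosen by a p-value rests on none of these assumptions.

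**What to change.** Delete the significance trigger in both Concomitant treatments and Statistical analysis, and state one primary model in advance. If concomitant treatment is to be a covariate, use only the regimen recorded before randomisation, name and code it beforehand, and include it whatever the between-group p-value. Tabulate treatment taken during the trial by arm. Any adjustment for it should be a sensitivity analysis, labelled as conditioning on post-randomisation data.

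This costs wording in the protocol and the analysis plan and leaves the total at 60. It should be settled before unblinding.

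A separate point remains. The Dropout criteria and the Concomitant treatments section say what happens to a patient whose treatment changes, and these must be reconciled with the definition of the full analysis set. Removing the trigger does not resolve that.

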#### Study design

This clinical study is a double-center, randomized, sham-controlled, patient- and assessor-blinded, and parallel trial. A total of 60 stroke survivors will be given both verbal and written forms of in-depth information about the trial by traditional Korean medicine (TKM) doctors before participation. All participants will voluntarily sign the informed consent that has been approved by the ethics committee prior to enrollment. Prior to allocation, the enrolled participants will be screened by the eligibility criteria.

After being randomly allocated into either the verum or sham EA group, in a 1:1 of allocation ratio, the participant will receive 9 sessions of verum or sham EA procedures for 3 weeks (3 sessions a week). The acupuncture regimen consists of 6 unilateral acupoints (LI4, LI15, TE14, SI9, SI11, and GB21) with electronic stimulation. Patients and outcome assessors will be blinded from the beginning of the study through completion.

The overall schematic chart and study schedule are shown in Figs. 1 and 2, respectively.

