#### Safety assessment

At every visit, assessors will ask a post-interventional question pertaining to adverse events. Unpleasant feelings regarding needling, dizziness, allergic reactions, slight pain, bruises, or pinpoint bleeding are expected on an individual basis. The intensity and causality of each adverse event will be evaluated and recorded. If serious adverse events occur, post-management will be properly carried out. The occurrences number of adverse events will be used for statistical analysis.

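### The safety analysis counts adverse event occurrences but pairs them with a chi-squared or Fisher test, which needs one yes/no result per participant

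*Protocol article*

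**What the plan says.** Two sections of the protocol article set the safety analysis.

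- **Safety assessment** describes repeated collection: "At every visit, assessors will ask a post-interventional question pertaining to adverse events". It lists mild reactions: "Unpleasant feelings regarding needling, dizziness, allergic reactions, slight pain, bruises, or pinpoint bleeding are expected on an individual basis". It then names the quantity to be analysed: "The occurrences number of adverse events will be used for statistical analysis".
- **Statistical analysis** repeats that quantity: "The number of adverse events will be presented with a 95% confidence interval on a safety set". The safety set is "defined as a subset of participants who receive at least one verum or sham treatment". The next sentence gives the comparison: "A chi-squared test or Fisher’s exact test will be carried out to compare the significant differences between groups". It does not say what is cross-tabulated.

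Study design gives the exposure over which events can accumulate: "the participant will receive 9 sessions of verum or sham EA procedures for 3 weeks". The Methods part of the abstract names the same two tests for safety and places them at the 5% significance level.

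No section defines a participant-level variable such as having at least one event, a denominator for the event count, or a method that allows for repeated events in one person.

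**The concern.** A chi-squared or Fisher test on a 2x2 table assumes that each entry is an independent unit falling in exactly one cell. Participants meet that condition, but occurrences of adverse events do not. Someone who bruises easily or finds needling unpleasant may report the same reaction at session after session, and those reports carry less information than the same number from different people.

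A raw count also has no complement. There is no natural number of non-events to put in the second column, and the count can exceed the number of participants.

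The safety comparison between verum and sham electroacupuncture is at stake. Analysed by occurrence, a few participants with repeated minor reactions could produce a nominally significant difference, and a confidence interval that treats events as independent would be too narrow. Safety appears beside effectiveness in the stated primary aim, so the comparison will be read as a result.

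**Working it through.** **Inputs from the protocol article.** 30 participants per arm (Power calculation); 9 sessions each (Study design); two-sided level 0.05 (Statistical analysis).

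**Inputs assumed.** The probability of an event in a session (5%, 10%, 20%) and the within-patient correlation ρ (0 to 0.5). The document gives neither.

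**Step 1: the plan's own figure.** The article states no number for the safety comparison beyond the 5% level. Its sample size, which supplies the 30 per arm, reproduces. The pooled SD is √((2.67² + 2.43²)/2) = 2.553 and the difference is 3.52 − 1.38 = 2.14. The normal approximation gives 23 per group; the t-based solution is 23.34, rounded up to 24. With 20% dropout, 24/0.8 = 30. This is not in dispute.

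**Step 2: can occurrences fill a 2x2 table?** With 30 × 9 = 270 sessions per arm and at most one event counted per session, the expected event totals are 270 × 0.05 = 13.5, 270 × 0.10 = 27 and 270 × 0.20 = 54. The last exceeds 30, so a table of events against participants without events would need a negative cell. A table can be formed only with another denominator. Sessions are the obvious candidate, but the article does not propose them.

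**Step 3: error rate if sessions are used.** For a cluster of 9 sessions the design effect is DE = 1 + (9 − 1)ρ. A test that ignores it has true two-sided error 2 × (1 − Φ(1.96/√DE)). At ρ = 0.2, DE = 2.6 and the error is 0.224. This was checked by simulating 20,000 trials per setting with beta-binomial events and no true difference. Ranges are over the three event probabilities.

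| ρ | DE | Formula | Session-level chi-squared | Session-level Fisher |
|---|---|---|---|---|
| 0 | 1.0 | 0.050 | 0.047–0.051 | 0.033–0.038 |
| 0.05 | 1.4 | 0.098 | 0.097–0.098 | 0.070–0.082 |
| 0.1 | 1.8 | 0.144 | 0.138–0.148 | 0.107–0.128 |
| 0.2 | 2.6 | 0.224 | 0.221–0.228 | 0.181–0.203 |
| 0.3 | 3.4 | 0.288 | 0.283–0.292 | 0.248–0.265 |
| 0.5 | 5.0 | 0.381 | 0.388–0.396 | 0.347–0.362 |

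**Step 4: another occurrence-based test.** Suppose instead that total events are tested against an even split between arms. With 0.5 to 2 events per participant on average, independent (Poisson) counts give 0.049–0.054. Overdispersed (gamma-Poisson) counts with shape 2 down to 0.5 give 0.079–0.377. The inflation is therefore not peculiar to the session-level table.

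**Step 5: the interval.** A naive interval has 1/√DE of the proper width: 0.75 at ρ = 0.1, 0.62 at 0.2 and 0.54 at 0.3.

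**Step 6: the participant as unit.** In the simulations of Step 3, comparing participants with at least one event out of 30 per arm gives an error of 0.046–0.057 by chi-squared and 0.015–0.029 by Fisher.

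**The case against.** The strongest reply is that the sentence naming the test does not name its table. The safety set is a set of participants, and the usual use of these tests on such a set is participants with an event against those without. On that reading the test is sound and only the description is loose. An article also condenses the full protocol, which may define the variable properly.

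Part of this stands. A participant-level test may well have been intended. But the article is not silent on the unit: both sections name the event count, and one says that the count is what will be analysed. The same Statistical analysis section speaks of numbers of participants when it describes the blinding table. Naming a safety set fixes who is included, not what is counted. If participants were meant, both sentences need the same correction.

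A second reply is that the inflation figures rest on a table, an event rate and a correlation that the article does not give. That is right, and at zero correlation there is no inflation. The figures show what happens if occurrences are tested; they do not estimate this trial's error rate.

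A third reply is that no true difference is an unlikely state for bruising or bleeding, because verum needles penetrate the skin and sham needles do not. This limits the weight of a false-positive rate for those events. It does not rescue the interval, which is too narrow under positive correlation whether or not the arms differ.

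Finally, a reader might infer that half of the trial's primary objective is compromised. The document does not support this. The primary aim mentions safety, but the hypothesis, the primary endpoint and the power calculation concern VAS alone.

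**Conclusion.** The point holds in a conditional form. The article names occurrences as the analysed quantity and pairs them with tests that need one independent yes/no per participant. Followed as written, the test's error rate and the 95% confidence interval would not be valid whenever events cluster within patients, which is plausible for needling reactions over 9 sessions.

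The size is illustrative. On the assumed session-level table, the chi-squared error runs from about 5% at correlation 0 to 29% at 0.3, with Fisher somewhat lower. A reader might infer that the planned safety test has an error rate of 14–29%. The document does not support that, because it specifies neither the table, nor the event rate, nor the correlation.

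The primary VAS analysis and the sample size are untouched.

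**What to change.** Amend both sections so that they name the same unit.

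- **Safety assessment:** state that the variable for the between-group comparison is whether a participant has at least one adverse event.
- **Statistical analysis:** state that the chi-squared or Fisher's exact test compares the number of participants with at least one event in the safety set, and give a 95% confidence interval for the risk difference.
- **Event totals:** report them descriptively by arm, or compare them as rates with a negative binomial model or a Poisson model with cluster-robust variance.

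The cost is a change of wording, provided that each event is recorded against its participant. The article says that the intensity and causality of each event are recorded but does not name the form; it mentions case report forms only for concomitant treatments. This should be confirmed.

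There is a small statistical price. The participant-level comparison ignores repeat events, which is why the totals should still be reported. Fisher's exact test is also conservative at 30 per arm (about 1.5–2.9% at a nominal 5% in the simulations), so it is less likely to detect a real excess of harm. The risk difference and its interval should therefore be read alongside the p-value.
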